### Baseline measurements

#### Questionnaire

The baseline questionnaire consisted of five parts and was sent back by mail in a pre-paid envelope before the initial appointment at the hospital.

Part one covered demographic variables such as name, address, age, gender, and e-mail address.

Information about medical history was collected by the second part of the questionnaire. Conditions related to risk factors for cardiovascular diseases were assessed using a series of questions according to the American College of Sports Medicine [25]. Questions about previous musculoskeletal complaints of the lower extremity and back were assessed per anatomical site. Open-ended questions were used to obtain information about body height (in cm) and body weight (in kg). These self-reported body height and weight data were used to calculate BMI (weight (kg)/height^2^(m)).

Sports participation was assessed in part three by using questions concerning type of sport and mean hours of sports participation. Furthermore, a question on running experience in the past ("Have you ever participated in running on a regular basis?") was used to assess the novelty to running.

Part four consisted of the Jenkins Activity Survey (JAS). The JAS is a tool to indicate type A behaviour [26]. Individuals with a pronounced type A behaviour, also referred to as coronary prone behaviour, are possibly more prone to injury [27]. Type A behaviour is characterized by above average achievement drive, aggressiveness, hostility, impatience, time urgency, and competitiveness [26].

Part five assessed the motivation for running, using a Dutch translated version of the Motivation Of Marathoners Scale (MOMS). The MOMS is an instrument that measures the motives of runners, by means of 56 items distributed across nine scales. Content areas covered include health orientation, weight concern, self-esteem, life meaning, psychological coping, affiliation, recognition, competition, and personal goal achievement. The MOMS was validated by Masters [28], and demonstrated an adequate internal consistency (Cronbach's alpha range .80 to .93), retest reliability (intraclass correlations range .71 to .90), and factorial validity of the scales.

#### Initial interview

During the initial interview at the UMCG all participants were seen by a sports medicine physician. The purpose of the initial interview was to screen for cardiovascular diseases and abnormalities of lower limb and, to ensure that the participants were adequately informed about the study before signing informed consent.

#### Orthopeadic examination

An universal goniometer with arm length 30 cm from axis to tip was used to measure all range of motions with recordings in increments of 1.0°. The internal and external range of motion of the hip was assessed with the participant supine and the tested hip and knee flexed to 90°. Knee flexion and extension ranges of motion were assessed with the participant in supine position. The goniometer was placed on the lateral aspect of the knee, with the axis of the goniometer in line with the greater trochanter and the lateral malleolus. Ankle plantarflexion and dorsiflexion were measured both with the knee fully extended and flexed to 90°. One arm of the goniometer was aligned with the fibular bone and the other with the plantar surface of the foot. Furthermore, the navicular drop was assessed by measuring the change in the height of the navicular tuberosity between a participant sitting with the subtalar joint in neutral position and participant standing, weight bearing with the subtalar joint in relaxed stance, as described by Brody [29]. The navicular drop is a valid method to indicate the amount of foot pronation [30]. Intratester and intertester reliability of this technique is ranging from .73 to .96 [31]. Measurements were made twice for each foot, with results being averaged.

### Randomization

After baseline measurements and informed consent, participants were assigned to the intervention training program or the control training program. To ensure that both training groups were equal in terms of injury risk, a stratified randomization was performed. Participants were stratified for current sporting activities status, previous injury, and gender. Based on sporting activities, there are three categories of novice runners. The first category consists of novice runners who already are participating in a sport in which axial load (i.e., running, walking or jumping) is integrated. The second category is formed by novice runners who already are participating in sporting activities without axial load, like swimming and cycling. The third category is formed by novice runners who did not participate in any sporting activities at baseline measurements. In a study by Macera [6], a 74% increased risk was found in runners with a positive history of previous injuries. Since it is not clear whether the high rate of re-injury is caused by incomplete healing of a previous injury or a biomechanical problem, a differentiation in time is made. A distinction can be made between no previous injury, sustaining injured in the last 12 months before baseline measurements, and sustaining injured more than 12 months before baseline measurements. Eighteen strata were formed by gender, previous injury (no, 3–12 months and > 12 months) and sporting activities (no, with axial load and without axial load). From each stratum participants were allocated to intervention or control group by drawing a sealed opaque envelope. Each stratum box contained equal numbers of control and intervention envelopes.

### Participant flow

The study design and participants flow are shown in Figure 1. A total of 603 people were interested to participate in the GRONORUN trial and reacted on the call for novice runners. All of those who responded to the advertisements were sent an information package containing: a brochure in which the study protocol was clearly described, a baseline questionnaire, and an appointment at the UMCG. Twenty three did not confirm their appointment for the initial appointment nor sent back the baseline questionnaire. Of those who confirmed the appointment for the initial appointment and sent back the questionnaire (n = 580), twenty five failed to attend the initial appointment. Of 555 persons who visited the UMCG for an initial appointment, 23 were excluded. Reasons for exclusion were: already participating in running (8), musculoskeletal injury of lower extremity or back at baseline (13) and contraindications for vigorous physical activity (2). After baseline measurements and stratification, 532 persons were randomly assigned to the intervention group (n = 264) and to the control group (n = 268).

### Training program

All participants received the same general written and oral information on intensity of running and on warming up and cooling down. Participants were instructed to walk brisk for 5 minutes as a warm up, and 5 minutes as cool down. Given that the best available evidence indicates that stretching before or after exercise does not prevent muscle soreness or injury [32], participants were instructed not to perform stretching exercises before, during or after the training sessions.

The frequency of running was equal in both groups. Each training week, except the last week, that is, the week of the four mile run, consisted of three training sessions represented by a combination of running and walking. Participants were encouraged to run on Monday, Wednesday, and Saturday, and were advised to run at a comfortable pace at which they could converse without breathlessness. Both groups trained individually, without a trainer, on a self-chosen course.

#### Control group: 8 week training program

The novice runners in the control group received a frequently used beginners training program to prepare for a four mile run. The program started 8 weeks before the start of the Groningen four mile run at the level of a run-walk session with a total of 10 minutes of running and 10 minutes of walking (see Table 1).

#### Intervention group: 13 week training program

The intervention group started the 10% rule training program 13 weeks before the start of the Groningen four mile running event (see Table 2). Gradual increase of training load, that is, time of running was 10% per week and the ratio between running and walking was also increasing. The starting point of the program was exactly the same as the start of the program of the control group (i.e., ten minutes of running, interchanged with walking).

### Outcome measures

The primary outcome of the GRONORUN trial is the number of RRI's in both groups. Definition of a RRI in this trial is; running related musculoskeletal ailment of the lower extremity or back, causing a restriction of running for at least one week, that is, three consecutive training sessions.

Information on RRI's and exposure data were collected using an internet based running log. Each of the participants received a study number and a password to enter a personal environment of the internet based training log. After each training week participants had to fill in their running activities, other sport activities and injuries.

Per training session the total minutes of running, total minutes of walking, and injuries were registered. Data on injuries were collected by registering anatomical site of the body and severity of pain. Severity of pain was subdivided in pain without limitation (no RRI), pain that caused a restriction of running (RRI), and running impossible through RRI (RRI). In case of skipping a training session, the reason (RRI, other injury, motivation, illness, or remaining reason) for it was asked. When a "running related injury" was the reason for not running, information on anatomical site and severity was asked. A picture of the lower body was used to assess the anatomical site of the RRI. By clicking on the anatomical site, the area of the RRI was red appointed. When participants did not enter their digital training log after one week, a reminder was sent by email automatically.

### Statistical analyses

To evaluate the success of the randomization, baseline values will be analyzed for differences between intervention group and control group, using a chi-square for categorical data and a student's t-test for numerical data. To analyze the primary outcome (i.e., RRI), the Kaplan-Meier method will be used. Once a participant has a RRI his or her survival time will be terminated. To evaluate the effect of the intervention, a log rank test will be used to compare the Kaplan-Meier curves of the intervention group to the control group. Analyses will be performed following the "intention to treat" principle. Differences will be considered statistically significant at p < 0.05. All analyses will be done using SPSS version 12 (SPSS, Chicago, Illinois).

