### Sample size

A power calculation was carried out for the main outcome variable RRI, using a logistic rank survival power analyses. In other studies on novice runners incidence of RRI varies from 29.5 to 58% in a periods of respectively 13 to 28 weeks [3,8]. For the GRONORUN trial we expected an injury incidence of 30%. With a hypothesized 25% reduction of RRI's in the intervention group compared to the control group, a total of 436 runners (2 × 218) were needed for a power of 80% and an alpha of 0.05. The hypothesized reduction was based on clinical relevance, because no other studies on the prevention of RRI in novice runners were found. Assuming an attrition of 15% in the intervention period, a total of 512 (2 × 256) novice runners were needed to detect an effect of the intervention.

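### The primary log-rank test ignores the three randomisation strata; it is valid but slightly conservative, and accounting for the strata is a small, cheap improvement

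*Protocol article*

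**What the plan says.** Under Randomization the article explains why it stratified: "To ensure that both training groups were equal in terms of injury risk, a stratified randomization was performed". It names the factors, "Participants were stratified for current sporting activities status, previous injury, and gender", and crosses them: "Eighteen strata were formed by gender, previous injury (no, 3–12 months and > 12 months) and sporting activities". The only strength given for any of them is for previous injury, where it cites a study in which "a 74% increased risk was found in runners with a positive history of previous injuries". On the mechanism it says "Each stratum box contained equal numbers of control and intervention envelopes"; it gives neither a block size nor the number of envelopes per box.

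Under Statistical analyses the primary comparison is stated as "To evaluate the effect of the intervention, a log rank test will be used", applied to the two arms' Kaplan-Meier curves. No strata and no covariates are attached to that test.

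**The concern.** The design treats the three factors as carriers of injury risk and the primary analysis then leaves them out. When allocation is balanced within prognostic strata, differences between strata contribute little to the difference between arms. The plain log-rank variance still counts them. The test statistic therefore varies less than its nominal standard deviation of 1, the true significance level falls below 5%, and some power is lost.

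What is at stake is efficiency, not validity. The useful question is how much power is lost on the article's own inputs.

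**Working it through.** **Inputs from the article.** 532 randomised (264 and 268); 13 weeks of follow-up; 30% expected incidence; 25% reduction, read as relative, so 30% to 22.5%; 15% attrition; significance at 0.05; 1.74 as the hazard ratio for previous injury.

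**Assumptions.** Stratum shares are not given. Used here: gender 40/60, previous injury 40/25/35 (none first), sporting activity 40/30/30. Dropout is exponential. All prognostic effects other than 1.74 are assumed.

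**The plan's own figures.** The article gives no figure for the gain from stratification. The nearest is the sample size, from which the effect size is taken: HR = ln(0.775)/ln(0.70) = 0.715. At that hazard ratio, 80% power and two-sided 0.05, Schoenfeld's formula needs 279 events. With mean incidence (0.30 + 0.225)/2 = 0.2625, that is about 1,063 runners; Freedman's formula gives about 1,082. The stated 436 does not reproduce. That is a separate matter, but it explains why the power figures below are near 47%. The attrition step does reproduce within rounding (436/0.85 = 513, stated as 512).

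**Step 1, size of the conservatism.** Let R² be the share of the log-rank score variance that lies between strata. With exact balance the plain statistic has standard deviation √(1 − R²), and the true level is 2 × [1 − Φ(1.96/√(1 − R²))].

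With 1.74 for any previous injury and nothing else, incidence is 22.1% without and 35.3% with previous injury (0.4 × 0.221 + 0.6 × 0.353 = 0.300). A hand check ignoring dropout gives R² ≈ 0.4 × 0.6 × (0.353 − 0.221)² / (0.30 × 0.70) = 0.00418/0.21 = 2.0%. The numerical value with dropout is 1.8%. Then √(1 − 0.018) = 0.991, 1.96/0.991 = 1.978, and the true level is 0.048.

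**Step 2, simulation of the plain against the 18-stratum log-rank test** (532 runners, blocks of 4 within strata):

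| Prognostic strength | R² | Level by formula | Simulated level, plain / stratified | Power at HR 0.715, plain / stratified |
|---|---|---|---|---|
| None | 0 | 0.050 | 0.054 / 0.056 | 47.4% / 47.2% |
| Previous injury 1.74 only (documented) | 1.8% | 0.048 | 0.0485 / 0.0503 | 47.1% / 47.5% |
| Moderate: 1.74; gender 1.3; sport 1.3 and 1.5 (assumed) | 3.1% | 0.0465 | 0.0503 / 0.0532 | 46.7% / 47.8% |
| Strong: 2.0 to 2.5 (assumed) | 10.5% | 0.038 | 0.041 / 0.051 | 43.3% / 47.6% |

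Simulation error is about 0.0015 to 0.002 on the level and 0.5 to 0.7 points on power. The documented gain of 0.4 points is therefore within the error of either figure. In the moderate case both simulated levels lie above the formula, but the gap between the tests (about 0.003) has the expected sign. At HR 0.60 the strong case gives 76.0% against 79.2%. A second simulation gave 47.1% against 47.4% in the documented case, about 1 point in the moderate case and 3 to 5 points in the strong case.

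**Step 3, looser balance.** If each box held equal numbers but was only partly used, the arms need not balance closely within strata. Drawing from such a box, power at HR 0.715 was 46.5% for both tests (documented), 45.9% against 46.1% (moderate) and 41.3% against 44.8% (strong). The plain test's level in the first two cases was 0.049 and 0.051.

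**Step 4, cost of stratifying.** Crossing the factors leaves 532/18 ≈ 30 runners and 532 × 0.2625/18 ≈ 8 events per cell. If the factors do not predict injury, the stratified test loses up to about 1 point (79.6% against 78.5% at HR 0.60, part-used boxes).

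**The case against.** The strongest reply is that the planned test is valid and errs on the safe side, and that on documented inputs the loss is too small to separate from simulation error. That stands, and it sets the severity.

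It can also be said that the three factors are not shown to be strong. No risk figure is given for gender or sporting activity. Of the four injury-related factors listed in the Background, only previous injury is a stratifier. Because recent lower-extremity injury is an exclusion criterion, the 74% may not carry over unchanged. This stands too: the losses of 3 points or more rest on assumption.

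A condensed article may leave covariates, adjusted estimates and confidence intervals to a fuller plan. Their absence is therefore not criticised here. The primary test, however, is named, and as worded it is unstratified. If a fuller plan already stratifies it, the point falls away.

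Several stronger readings are tempting but unsupported:

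- A reader might infer that ignoring the strata inflates false positives. The effect runs the other way.
- A reader might say the plan yields only a p-value. Kaplan-Meier estimation in each arm is planned.
- A reader might say the unadjusted comparison understates the effect. Marginal and conditional hazard ratios are different quantities, and reporting the marginal one is not an error.

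**Conclusion.** The mismatch between design and analysis is real, and its direction is clear: with prognostic factors and balance within strata, the plain log-rank test is slightly conservative. The size is small. At HR 0.715 the power loss is well under 1 point on the only documented strength, about 1 point if all three factors are moderately prognostic, and about 3 to 5 points only if they are strongly prognostic. The article does not show the last two. These figures rest on assumed stratum shares and on close balance within strata; part-used boxes reduce the loss.

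A reader might link this point to the shortfall in the stated sample size and expect the change to recover it. It would not: with or without stratification, power at HR 0.715 stays near 47% in the documented case. Low severity: a near-costless improvement, not a flaw that threatens the conclusion.

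**What to change.** In the Statistical analyses section, have the primary test account for the randomisation factors, and fix one of two forms in advance:

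- a log-rank test stratified by gender, previous injury and sporting activity, in the categories used for allocation (18 cells when crossed); or
- the treatment test from a Cox model with the three factors as main effects, which avoids sparse cells.

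Keep the plain log-rank test and the Kaplan-Meier curves as supportive.

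The cost is one sentence and no new data, since each participant's stratum was known before the envelope was drawn. There are two small downsides. The 18-cell test can lose up to about 1 point of power if the factors are not prognostic. A Cox estimate assumes proportional hazards, which deserves a check because the two programmes start 13 and 8 weeks before the event. The simulations above compare the plain and 18-stratum log-rank tests; the main-effects Cox test was not simulated.

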## Background

Worldwide, running is a sport practiced by many individuals to improve cardio-respiratory function, health and well-being [1]. The Royal Dutch Athletics Federation (KNAU) has estimated that around 12.5% of all Dutch people are running on a regular basis, and that the popularity of running events is still growing. The popularity of running positively contributes to increasing levels of physical activity in the population. This is important, because physical inactivity is associated with the development of several chronic diseases, decreased longevity, loss of physical function and weight control [2]. Running is a feasible way for people to become more active. To start with running, just a pair of shoes is needed.

Although running positively contributes to health, there is also the possibility of a running related injury (RRI). The incidence of RRI's injuries in runners at recreational and competitive level is high and varies from 30% to 79% [3-9]. The wide range in incidence is caused by 1) differences in injury definition, 2) time of follow up, 3) differences in population at risk, and 4) differences in methods used to assess RRI, as well as exposure to running. Taking into account the exposure to running, an appropriate way to describe the incidence of RRI's is to calculate the number of RRI's per 1000 hours of running in the population at risk. Injury incidence per exposure varies from 7 to 59 per 1000 hours of running [3-5,10].

Most injuries in runners are overuse injuries of the lower extremity, caused by training errors, that is, running too much, too soon [11]. The exact cause and risk factors of RRI's are still unclear. However, it can be stated that the aetiology of these injuries is multifactorial and diverse. A review by Van Mechelen [12] proposed four factors that have been significantly related to running injuries: a) lack of running experience, b) previous injury, c) running to compete, and d) excessive weekly running distance.

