## Methods/design

The GROningen NOvice RUNing (GRONORUN) study is a randomized controlled trial (RCT) with a thirteen week follow-up. Participants were randomized into an intervention group (13 weeks training program) or an active control group (8 week training program). Recruitment of participants for the GRONORUN trial took place in May and June 2005 and data collection started in July 2005. The intervention training program started in the second week of July, 13 weeks before the four mile running event, which took place in October 2005.

The study design, procedures and informed consent procedure were approved by the Medical Ethics Committee (Number 2004/285) of the University Medical Center Groningen (UMCG), The Netherlands. All participants provided written informed consent. Guidelines were followed according to the Consort Statement [24].

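### The primary log-rank test has no stated time origin although the programmes last 13 and 8 weeks, so its result can depend on the time scale

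*Protocol article*

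**What the plan says.** The two programmes end at the same event but start at different times. For the control arm, "The program started 8 weeks before the start of the Groningen four mile run". For the other arm, "The intervention group started the 10% rule training program 13 weeks before the start of the Groningen four mile running event".

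The Methods/design section gives one follow-up period for the whole trial: the study "is a randomized controlled trial (RCT) with a thirteen week follow-up". The abstract likewise has participants keeping their log over thirteen weeks.

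The primary analysis is time to first running related injury (RRI). The Statistical analyses section states that "Once a participant has a RRI his or her survival time will be terminated" and that "a log rank test will be used to compare the Kaplan-Meier curves of the intervention group to the control group", under intention to treat. It does not say whether time runs from the common start, from randomisation or from each arm's own programme start. It does not mention the five extra training weeks.

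On exposure, the Background says that "an appropriate way to describe the incidence of RRI's is to calculate the number of RRI's per 1000 hours of running", as a way of describing incidence. The Outcome measures section records the data for it: "Per training session the total minutes of running, total minutes of walking, and injuries were registered". The stated test does not use them.

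**The concern.** A log-rank test compares, at each moment, the arms' injury rates among those still at risk on the chosen clock. Here two clocks are possible and they compare different things.

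- **Own programme start.** Controls have no observation after week 8. Intervention injuries in weeks 9 to 13 then have no comparator and add nothing to the statistic. Under the 10% rule these are the weeks of highest running time.
- **Common start of the 13-week follow-up.** For the first five weeks, controls are in the risk set with no scheduled running. Afterwards the shorter programme concentrates their injuries into eight weeks. The hazards are non-proportional by design.

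If the clock is not fixed in advance, the significance of the primary result, and sometimes its direction, rests on a choice that could be made after the data are seen.

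**Working it through.** The plan gives no figure on this point to reproduce. Its sample size is a separate matter.

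**Inputs.** Programme lengths of 13 and 8 weeks (training program sections). 532 randomised as 264 and 268, so 266 per arm on average (Participant flow). Expected incidence 30%, taken here as control risk by race day, and a 25% reduction, 30% × 0.75 = 22.5% (Sample size).

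**Assumptions.** Constant weekly hazard within a programme, zero control hazard before the control programme starts, no dropout, two-sided 0.05.

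**1. Hazards under equal 30% race-day risk.** Cumulative hazard is −ln(0.70) = 0.3567. Control: 0.3567/8 = 0.0446 per week. Intervention: 0.3567/13 = 0.0274 per week. Each arm expects 266 × 0.30 = 79.8 injuries.

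**2. Own-start clock.** By week 8 the intervention risk is 1 − exp(−8 × 0.0274) = 0.197, or 52.4 injuries. The other 79.8 − 52.4 = 27.4 fall in weeks 9 to 13 and are lost to the test. The intervention share of the risk set rises from 0.500 to 0.803/(0.803 + 0.700) = 0.534. About 68.2 of the 132.2 counted injuries are then expected there. Observed minus expected is −15.84, with variance 33.01, so z = −15.84/√33.01 = −2.76. The chance of a significant benefit is Φ(2.76 − 1.96) = 0.79. Simulations gave 77% to 80% with constant hazard and about 98% with hazard proportional to an assumed ramp in running time.

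**3. Common 13-week clock, same truth.**
- Weeks 1 to 5: 34.1 intervention injuries, none in control, 16.5 expected, difference +17.6.
- Weeks 6 to 13: 45.7 and 79.8 injuries, 60.5 expected in the intervention arm, difference −14.8.
- Sum +2.83, variance 39.83, z = +0.45.

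The chance of significant harm is Φ(0.45 − 1.96) = 0.065, and of benefit Φ(−0.45 − 1.96) = 0.008. Simulations gave 6% to 8% and 1%. A race-day comparison of cumulative incidence rejects in about 5%.

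**4. Power for 30% against 22.5%.** Intervention hazard is −ln(0.775)/13 = 0.2549/13 = 0.0196 per week.
- Log-rank on the common clock: difference −9.59, variance 34.88, z = −1.62, power Φ(1.62 − 1.96) = 0.37.
- Race-day comparison: standard error √[(0.30 × 0.70 + 0.225 × 0.775)/266] = 0.0380, z = 0.075/0.0380 = 1.97, power about 0.50.

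**5. All scenarios at 266 per arm** (share of trials significant)

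| Truth (intervention v control injured by race day) | Log-rank, own start | Log-rank, common clock | Race-day comparison |
|---|---|---|---|
| Equal, 30% v 30% | benefit 79% | harm 6–8%, benefit 1% | about 5% in total |
| Planned, 22.5% v 30% | benefit 99% | benefit 36–37% | benefit about 50% |
| Weekly hazard 25% lower, 35.3% v 30% | benefit 40–41% | harm 44–46% | harm 25% |
| Equal weekly hazard, 44.0% v 30% | about 5–6% in total | harm 98% | harm 92% |
| Equal hazard per running minute (assumed ramps), 44% v 30% | benefit 36–50% | harm 97–98% | not run |

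The race-day risks in rows 3 and 4 are 1 − exp(−0.75 × 0.3567 × 13/8) = 35.3% and 1 − exp(−0.3567 × 13/8) = 44.0%. The mean z changes sign in row 3 (−1.71 to about +1.8) and row 5 (−1.65 to −1.97, against +3.8 to +3.9). In rows 1 and 4 the change is between a clear effect and roughly none. In row 2 the direction holds and only power changes.

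**The case against.** The strongest reply is that the article already points to the common clock. It gives one thirteen-week follow-up for the trial and an intention-to-treat analysis, and it nowhere mentions timing from each arm's own start. A condensed article may also leave the time origin to a fuller document. Most of this stands. The common clock is the more natural reading, so the 77% to 98% figures show what an own-start clock would do, not what the plan says it will do.

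A reader might also infer that the common clock produces a false harm when weekly hazards are equal. The documents do not support that. With equal weekly hazard, 44.0% against 30% are injured by race day, which is a real excess on the quantity the trial sets out to compare. The race-day comparison finds it too, in 92% of trials.

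Nor does the Background make injuries per 1000 running hours the required measure. It calls this an appropriate way to describe incidence, and exposure arises after randomisation.

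The reply does not remove the point. The article fixes the test, and naming the common clock alone leaves that test non-proportional by design, slightly tilted under equal race-day risk and weaker than a race-day contrast.

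**Conclusion.** The concern holds in a limited form. A plain log-rank test without a stated origin, applied to programmes of 13 and 8 weeks, can give different results on different clocks, and opposite ones in some scenarios. That it always gives opposite answers is a tempting inference, but rows 1, 2 and 4 of the table do not show it.

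On the more natural reading the cost is moderate: a tilt toward harm under equal race-day risk (about 6% to 8% against 1%) and power of about 37% where a race-day contrast has about 50%. On an own-start clock the error would be severe.

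The figures rest on no dropout, although the plan allows for 15% attrition, and on zero control hazard in the first five weeks. Any running by controls in that period would shrink the lean toward harm. The load-based figures, including the upper 98%, rest on assumed ramps because the training tables are not shown.

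Two further inferences lack support. Nothing in the article shows that runners quit more often in the longer programme. The planned 25% reduction is of injuries and is not stated as a weekly hazard ratio, so it cannot be faulted as one.

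**What to change.** In the Statistical analyses section:

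- Set time zero for every participant at the common start of the 13-week follow-up.
- Make the primary contrast the Kaplan-Meier cumulative incidence of first RRI at race day, reported as a difference with a 95% confidence interval and a test.
- State that a log-rank test timed from each arm's own programme start will not support the effectiveness claim.
- Optionally, add first RRI per 1000 running hours from the log as a supportive analysis, with a note that exposure is post-randomisation.

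The cost is a small change of wording and some programming, since all the data are already collected. If the per-hour analysis is added, there is a second measure to interpret, and it may not agree with the first.
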